## Abstract

**Background:**

Pregnancies in women with pre-existing medical conditions are on the rise. These pregnancies are characterized by an increased rate of maternal and perinatal complications, which can result in higher health care expenditures and altered pregnancy experiences. The purpose of this study is to integrally analyze maternity care for women with pre-existing conditions in the framework of a risk-adapted, interdisciplinary care by recording three substantial parts of maternity care: (1) maternal and perinatal outcome; (2) hospital costs and reimbursements covering the period from preconception counseling or initial antenatal visit to discharge after birth; and (3) women’s experience of reproductive choice and becoming a mother in the presence of a pre-existing condition.

**Methods:**

In this observational, prospective, longitudinal, and monocentric cohort study, we aim to include a total of 1,500 women over a recruitment period of 15 months. Women registering for care at the Department of Obstetrics and Prenatal Medicine, University Hospital Bonn, Germany, are allocated to three groups based on their health and risk status: women with pre-existing conditions, as well as healthy women with obstetric risk factor and healthy women with a low-risk pregnancy. Participants are observed from time of initial consultation until discharge after birth. Analysis focuses on (1) maternal and perinatal outcome, especially rate of severe maternal and neonatal morbidity; (2) costs and reimbursements; and (3) surveys to capture of women’s experience and health-related quality of life during the time of reproductive choice, pregnancy, and childbirth in the presence of pre-existing medical conditions.

**Discussion:**

With its complex three-dimensional design, the ForMaT-Trial is aiming to provide a comprehensive analysis of pregnancy and childbirth in women with pre-existing conditions. The results may serve as a basis for counseling and care of these women. By analyzing costs of specialized care, data for discussing reimbursement are generated. Lastly, our results may increase awareness for the perception of reproductive choice, pregnancy and motherhood in this continuously rising population.

**Clinical trial registration**: German Clinical Trials Register, DRKS00030061, October 28, 2022.

## Introduction

1

### Background and rationale

1.1

The number of pregnancies in women with pre-existing medical conditions has increased over the last decades (1–3). A Danish registry study of more than 1.3 million births found an increase in the prevalence of maternal chronic conditions over a period of 25 years from 3.7% in 1989 to 15.7% in 2013 (1).

Three main factors contributing to this ongoing trend can be identified. First, the shift to delay childbearing resulting in advanced maternal age is associated with a higher prevalence of chronic conditions, such as cardiovascular diseases, obesity, or diabetes (4, 5). Second, advances in the treatment of severe childhood conditions result in higher life expectancy of affected women, who enter adulthood and may consider pursuing pregnancy. Improved survival rates of childhood, adolescent, and young adult’s cancers (6) or of newborns with congenital heart disease (7–9) may serve as examples. Lastly, progress in assisted reproductive technologies allows pregnancies in women with reduced fertility due to their advanced maternal age or pre-existing condition (10).

Pregnancies in women with pre-existing conditions represent high-risk pregnancies and bear the risk of high-risk deliveries (11, 12). Maternal complications during pregnancy and childbirth, whether they occur because of the underlying chronic condition, obstetric risk factors, or both, may result in severe maternal morbidity (SMM) (12, 13). SMM is defined as a spectrum of complications during pregnancy, childbirth, and postpartum, which results in significant short-or long-term health issues for women including maternal death (14–16). The reasons for higher rates of adverse pregnancy outcomes in women with pre-existing conditions arise from the interactions of chronic disease and pregnancy itself. These may vary upon the underlying condition: While cardiac or renal conditions tend to deteriorate during pregnancy (17, 18), women affected by rheumatic disease or multiple sclerosis often enjoy a relapse-free time during pregnancy but are at risk of suffering from flares in the postpartum period (19–21). However, SMM not only affects maternal health but may also lead to perinatal morbidity and mortality. The spectrum of perinatal consequences includes prematurity, neonatal intensive care unit (NICU) admission, low birthweight, low APGAR-score, or perinatal death (11, 22, 23). Additionally, women with chronic health conditions may require long-term medication, but inadvertent intake of teratogenic or fetotoxic substances may negatively impact the intrauterine development. However, continuation of disease-specific medication is often indispensable for the women’s health (24).

For the above-mentioned reasons pregnancies and deliveries in women with pre-existing conditions are known to entail higher health care expenditures. Risk-adapted antenatal care may cause additional costs on the one hand, but expenses may be saved because of averted complications of childbirth (25). In Germany, reimbursement of antenatal care performed by hospital outpatient departments is regulated by the German Federal Joint Committee (26). However, costs for the time-and intervention-intensified risk-adapted maternity care in women with pre-existing conditions are likely to exceed this reimbursed sum.

A further aspect related to this topic involves the experience of becoming a mother in the presence of a pre-existing condition. The perception of pursuing pregnancy and becoming a mother has been investigated for specific conditions and in small sample sizes (27–30).

The management of pregnant women with pre-existing conditions requires knowledge of the interactions between chronic condition and pregnancy. The German maternity guidelines provide detailed instructions on the obstetric and fetal surveillance but lack specific instructions for counseling and treatment of women with pre-existing conditions (31). Furthermore, the understanding and management of chronic conditions during pregnancy, childbirth and postpartum period is being taught in the growing field of Obstetric Medicine as a subspeciality of internal medicine in only few countries, such as Canada, Australia and the United States of America (32). In Germany, only few university hospitals hold outpatient consultations for specific diseases in pregnancy but specialized sections covering all medical conditions are not yet established. At the Department of Obstetrics and Prenatal Medicine, University Hospital Bonn, Germany, women with pre-existing conditions are cared for within the frame of a specialized consultation. This includes preconception counseling and care during pregnancy, childbirth, and the puerperium within an interdisciplinary framework.

### Study aim

1.2

This study is designed to describe risk-adapted maternity care for women with pre-existing conditions on a medical, economic, and psychological level. By assessing rate of SMM among this special population data will be generated which may serve as a basis for recommendations of the care of women with pre-existing conditions during reproductive choice, pregnancy and postpartum period. Consequently, establishing a framework for the care of affected women is aim of this study. Furthermore, by capturing and analyzing costs and reimbursement of specialized care, data will be generated which may serve as basis for discussion with the relevant bodies. Lastly, the special perceptions and needs of affected women will be elucidated to provide care givers with evidence and to increase awareness for this steadily increasing group of patients.

### Objectives

1.3

The objectives of this three-dimensional study include the assessment of:

maternal and perinatal outcome with a special focus on the SMM rate;services and associated costs covering the period from preconception counseling or initial antenatal visit to discharge after birth;women’s experience of reproductive choice and becoming a mother in the presence of a pre-existing condition.

## Methods

2

### Trial design and study status

2.1

This study is designed as an observational, prospective, longitudinal single-center cohort study. Recruiting and data collection started in November 2022 and is scheduled to last until January 2024. Observation of participants covers the period from preconception counseling or initial consultation in pregnancy to hospital discharge after birth. Assignment to study and comparative groups is applied during recruiting.

This protocol is structured in accordance with the guidelines of Standard Protocol Items: Recommendations for Interventional Trials (SPIRIT)-Patient-Reported Outcomes (PRO)-Extension (33–35), although it is not considered an interventional trial. This extended version addresses the importance of patient-centered care by implementing recommendations to correctly document PRO in clinical trial protocols. In addition to this specific protocol writing guideline, we also applied aspects of the Strengthening the Reporting of Observational Studies in Epidemiology (STROBE) guidelines as this study is designed as an observational cohort study (36, 37).

Note on language usage: in this work we use the terms “woman/women” to refer to individuals with a uterus and the biological capacity to become pregnant.

### Study and health care setting

2.2

Study center is the Department of Obstetrics and Prenatal Medicine, University Hospital Bonn, Germany, which serves as a regional referral center and has a unique standing in Obstetric Medicine. The specialized outpatient department “Obstetric Medicine” cares for an increasing number of women with pre-existing medical conditions, which shapes the obstetric patient population and medical education at the department. It routinely interacts with related medical subspecialities and closely cooperates with the Center for Rare Diseases of the University Hospital Bonn.

All women presenting at the study center receive the same risk-adapted obstetric care during pregnancy and childbirth, irrespective of their participation in the study. While women with pre-existing conditions may require more frequent follow-up, interdisciplinary management, case conferences, and additional diagnostic investigations compared to healthy women with obstetric complications, healthy, “low-risk” women register for birth via a midwife appointment. This type of risk-adapted care is the standard of care at the study center and therefore is not considered a classical study intervention.

### Eligibility criteria

2.3

Women in all stages of pregnancy and women seeking preconception counseling who present at the study center can be included in this study if they meet the inclusion criteria and provide informed written consent. All participating women must be capable to fully understand the study requirements and intentions. The study group (S) is compared to two additional groups (K1 and K2). The inclusion criteria vary as follows.

#### Study group S

2.3.1

Women with pre-existing medical conditions, presenting either pregnant or for preconception counseling, are invited to join the study. For our study, we defined pre-existing condition as the presence of chronic diseases (e.g., multiple sclerosis) or of sequelae of a preceding health incident (e.g., history of pulmonary embolism). A list of included conditions can be found in Supplementary Table 1. It is important to emphasize the fact that only severe conditions, which may have an impact on the course of pregnancy and/or delivery and/or on women’s perception of pregnancy are included. Therefore, pre-existing conditions which appear to be irrelevant for pregnancy outcome and women’s perception are explicitly excluded. For the latter, in Supplementary Table 2, we provide a list of conditions considered to be irrelevant for our investigation, meaning that women exclusively fulfilling these diagnoses are not included in the study (e.g., essential hypertension without medication before pregnancy). Both selection processes were undertaken by consensus meetings of the research team. Uncertainties regarding inclusion or exclusion of rare or exceptional cases are resolved in a consensus meeting with two Obstetric Medicine experts on a case-by-case decision (e.g., sarcoidosis without functional impairment).

Women in study group S are required to understand and complete the questionnaires in German language. If a woman is willing to participate in the study but not capable to complete the questionnaires due to language barriers, recruitment is possible for analysis of medical outcome and economic evaluation only.

#### Additional group K1

2.3.2

Healthy pregnant women whose pregnancies are considered at-risk due to their obstetric history or findings during the current pregnancy (e.g., gestational hypertensive disorders, gestational diabetes, and previous cesarean section) are enrolled. No maternal pre-existing condition, except for uncomplicated, substituted hypothyroidism, must be present. A list of all pre-defined obstetric conditions and complications is provided in Supplementary Table 3.

#### Additional group K2

2.3.3

Healthy pregnant women with a singleton fetus in cephalic presentation who register for birth at term after an uneventful course of pregnancy—i.e., low-risk women expecting an uncomplicated vaginal delivery—are invited for study participation as a second comparative group. No maternal pre-existing condition or obstetric complication, except for substituted hypothyroidism, must be present.

#### Exclusion criteria for all groups

2.3.4

Women presenting with higher-order multiple pregnancies (more than twin pregnancy) and women who are not capable to understand the study intention are not enrolled. Furthermore, healthy women referred for care at our institution because of fetal anomalies (e.g., aneuploidies, malformations) are not included in the study.

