### Outcome measures

2.7

The three-dimensional design of the ForMaT-Trial indicates three different outcome measures as follows:

The primary medical outcome is SMM. For its assessment, a list with previously defined indicators can be found in Table 1. It was adapted from the Centers for Disease Control and Prevention (CDC) (15) after a thorough literature review. Maternal secondary outcome measures consist of complications of pre-existing disease or obstetric complications, mode of delivery, type of anesthesia, length of hospital stay for delivery, and need for transfusion >4 units of packed red blood cells (PRBC). Perinatal secondary outcome measures are late miscarriage (>14 weeks of gestation), intrauterine fetal death, gestational age at birth, birthweight with percentile, APGAR-scores, arterial umbilical cord pH, severe neonatal complications including transfer to NICU, length of stay in NICU, and death.In the second part of our study, an analysis of associated costs and reimbursement for study participants is undertaken. This includes the evaluation of billing and cost coverage of the in-and outpatient health sector and further associated costs.The third trial part captures the experience of pregnancy planning, pregnancy, and childbirth, as well as health-related quality of life in women with pre-existing disorders, which is assessed by questionnaires at predetermined time points (Figure 2). The questionnaires are a combination of pre-validated instruments and specifically designed questions. As validated PRO-instruments, the German version of the EQ-5D-5L™ is incorporated in each questionnaire (38) and the German version of the BSS-R (Birth Satisfaction Scale-Revised) is included in the postpartum questionnaire (39, 40). Table 2 provides an overview of item count, domains that are interrogated, and content of all four questionnaires. Questionnaires are only filled out by women in study group S. Timepoints are as follows (Figure 2): during the initial antenatal consultation at the study center; during the appointment for birth planning; and in the postpartum period before discharge from the maternity department. If the initial visit to the study center occurs after 34 weeks of gestation only one antenatal questionnaire is filled out. Recruited women seeking preconception counseling are also asked to fill out a questionnaire after the appointment.

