### Statistical analysis

2.10

All medical parameters will be summarized using descriptive statistics. The primary medical outcome will be analyzed with a conditional logistic regression model to assess the effects of pre-existing medical conditions on the SMM rate. Odds ratios obtained from this model with corresponding 95% confidence intervals will be reported. Further secondary medical maternal and perinatal parameters will be compared between the study and additional groups. Additional analyses of medical parameters will be considered in subgroups given by different pre-existing conditions in the study group and are exploratory in nature. The main analysis will be performed on complete cases and the significance level will be set to 0.05. A sensitivity analysis will include the use of multiple imputation strategies to address possible missing observations.

For analysis of costs, a health economic evaluation to determine the costs associated with the interventions and services in the different groups will be conducted. This includes, for example, consultation time, laboratory tests, medical procedures, hospitalization, or medication. The resource use of implemented care of all the three groups will be captured, both for inpatient and outpatient setting. Thereafter, this resource use will be multiplied times unit prices to derive respective costs from a provider (in-and outpatient healthcare provider) and healthcare system perspective (statutory health insurance).

The items of the questionnaires will be summarized descriptively at each time point. Health-related quality of life will be analyzed as pre-specified in the manual of the EQ-5D-5L™ tariff and compared over time (42). The birth experience assessed by the German version of the BSS-R will be reported via the total score and the three subscales (stress during labor, personal attributes, and quality of care provision) (39).

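### Women referred because of a fetal anomaly are kept out of K1 and K2 but not out of S, so the secondary perinatal comparisons, mainly S versus K1, tilt against S by an amount the protocol does not fix

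*Protocol article*

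**What the plan says.** Section 2.3.4 of the protocol article is headed "Exclusion criteria for all groups". Its first sentence fits that heading and carries no restriction by health status: "Women presenting with higher-order multiple pregnancies (more than twin pregnancy) and women who are not capable to understand the study intention are not enrolled". The next criterion is narrower: "healthy women referred for care at our institution because of fetal anomalies (e.g., aneuploidies, malformations) are not included in the study".

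The group definitions decide whom the word healthy reaches:

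- S (2.3.1): "Women with pre-existing medical conditions, presenting either pregnant or for preconception counseling, are invited to join the study". No fetal criterion is given.
- K1 (2.3.2): "Healthy pregnant women whose pregnancies are considered at-risk due to their obstetric history or findings during the current pregnancy".
- K2 (2.3.3): "Healthy pregnant women with a singleton fetus in cephalic presentation who register for birth at term after an uneventful course of pregnancy".

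The perinatal secondary outcomes in 2.7 cover late pregnancy loss, fetal death, gestational age, birthweight, APGAR scores and cord pH, and end with "severe neonatal complications including transfer to NICU, length of stay in NICU, and death". Section 2.10 plans that "Further secondary medical maternal and perinatal parameters will be compared between the study and additional groups". Stratification (2.5) is by parity, plurality and recruitment setting. Fetal anomaly is not a factor.

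**The concern.** A woman with a pre-existing condition who is referred because of a fetal malformation or aneuploidy is eligible for S. A healthy woman referred for the same reason is barred from K1 and K2. The selection rule therefore differs by the exposure under study, on a factor that bears on most of the perinatal outcomes being compared.

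If anomaly pregnancies do worse, some of the excess in S will come from the enrolment rule rather than from the maternal condition. The abstract says the results may serve as a basis for counseling these women, so an overstated perinatal risk could reach patients.

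**Working it through.** **Text check.** Reading the sections together:

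| Group | Healthy by definition? | Anomaly-referral exclusion applies? |
|---|---|---|
| S (2.3.1) | No | No |
| K1 (2.3.2) | Yes | Yes |
| K2 (2.3.3) | Yes | Yes |

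The asymmetry follows from the criterion's own wording. The other two exclusions in 2.3.4 show that the authors wrote unrestricted criteria where they meant them. Nothing shown in 2.5 or 2.10 offsets the difference.

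**Direction and size.** The plan states no figure on this point, so there is none to reproduce. Let *a* be the share of S pregnancies with an anomaly, *b* the share in the comparison group, *r0* the risk of an adverse perinatal outcome without an anomaly and *ra* the risk with one. Assume the maternal condition has no effect, so that *r0* and *ra* are the same in all groups.

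- Risk in S = (1 − a)·r0 + a·ra
- Risk in the comparator = (1 − b)·r0 + b·ra
- Spurious difference = (a − b)·(ra − r0)

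The difference is positive whenever a > b and ra > r0. That settles the direction. The size depends on four quantities that the documents do not give, so everything below is assumed.

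With b = 0, the largest contrast the rule could produce for a given *a*:

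| a | Pregnancies of 600 in S | r0 = 10%, ra = 50% to 80%: risk in S | Risk ratio | r0 = 2%, ra = 20%: risk in S | Risk ratio |
|---|---|---|---|---|---|
| 1% | 6 | 10.4% to 10.7% | 1.04 to 1.07 | 2.18% | 1.09 |
| 3% | 18 | 11.2% to 12.1% | 1.12 to 1.21 | 2.54% | 1.27 |
| 5% | 30 | 12.0% to 13.5% | 1.20 to 1.35 | 2.90% | 1.45 |
| 10% | 60 | 14.0% to 17.0% | 1.40 to 1.70 | 3.80% | 1.90 |

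Example: a = 5%, ra = 50% gives 0.95 × 0.10 + 0.05 × 0.50 = 0.120, and 0.120 / 0.10 = 1.20. The 600 is 1,500 × 2/5, from the 2:2:1 ratio in 2.5.

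**Allowing anomalies in K1.** The criterion turns on reason for referral, so b need not be zero. Take a = 5% and b = 2% with r0 = 10%:

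- ra = 50%: K1 risk = 0.98 × 0.10 + 0.02 × 0.50 = 0.108; risk ratio = 0.120 / 0.108 = 1.11
- ra = 80%: K1 risk = 0.98 × 0.10 + 0.02 × 0.80 = 0.114; risk ratio = 0.135 / 0.114 = 1.18

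On these figures the spurious excess falls from 2.0 to 3.5 percentage points to 1.2 to 2.1 points.

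**The case against.** The strongest defense is that the asymmetry may be deliberate and partly right. S is enrolled because of the mother's own condition, and the aim (1.2) is to describe care for that population. The background section (1.1) notes that long-term medication can harm the fetus, so some anomalies in S may be a consequence of the condition or its treatment. Removing them would strip out real burden and could bias the comparison towards no difference. For healthy women the rule has a purpose too: without it, K1 in a prenatal-medicine department could fill with fetal referrals and stop being a group defined by obstetric risk. This stands. It is why removing anomaly referrals from S should not replace the all-S comparison. It does not make the all-S comparison sufficient alone, because that comparison cannot separate an anomaly caused by the condition from one that K1 would also have shown had it been allowed in.

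Three further limits stand. K2 is restricted to uneventful term singleton pregnancies and differs from S in perinatal risk by design, so the point bears mainly on S versus K1. Only secondary outcomes are touched. And the criterion is explicit about whom it excludes, so the heading is loose rather than misleading.

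The defense that this belongs in the analysis plan is only half right. How results are tabulated can wait for that plan, but the eligibility rule that creates the imbalance is fixed here.

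**Conclusion.** The point holds as a limited one. Section 2.3.4 applies an anomaly-referral exclusion to K1 and K2 but not to S, and if followed as written it shifts the secondary perinatal comparisons against S wherever anomaly pregnancies carry higher risk. The direction rests on that condition and on a higher anomaly share in S than in the comparator. The size cannot be derived from the documents.

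A reader might infer more than the text supports:

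- That anomalies occur in S only. A K1 woman enrolled for a previous cesarean section, say, whose fetus has an anomaly that was not the reason for referral is not excluded by this wording.
- That anomaly referrals are common in S. The article describes a regional referral center but gives no figure for women who also have a severe pre-existing condition.
- That the odds of perinatal death could double or triple. With a = 5%, b = 0, and an assumed death risk of 0.5% without and 10% to 20% with an anomaly, S would reach 0.95 × 0.005 + 0.05 × 0.10 = 0.98% to 0.95 × 0.005 + 0.05 × 0.20 = 1.48%, an odds ratio of 1.96 to 2.98. But every input is assumed, and in 600 women this is about 3 deaths becoming 6 to 9.
- That the whole excess is spurious. Part may be a true effect of the condition or its medication.
- That the primary result is compromised. Severe maternal morbidity, the sample size and the conditional logistic model concern the mother and are affected at most indirectly.

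**What to change.** 1. State in 2.3.4 that the fetal-anomaly criterion applies to K1 and K2 and not to S, and give the reason.
2. Record reason for referral as a flag for every S woman, taken from the referral as it stood at enrolment. Say beforehand how referrals with both a maternal and a fetal reason are coded.
3. Pre-specify that the S versus K1 and K2 perinatal comparisons are reported twice: for all S, and with S women referred because of a fetal anomaly removed, which is the rule K1 and K2 already follow. Attribute a difference to the maternal condition only in light of both results.
4. Keep all S women in the maternal, cost and questionnaire analyses. Keep anomalies first found after enrolment in every group.

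The cost is one flag, one extra analysis and slightly fewer S pregnancies in the restricted comparison. Recruitment was scheduled to end in January 2024 and the excluded healthy women were never enrolled. A remedy on the S side at analysis is therefore the practical one.
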